### Ethical Approval

All procedures have been approved by the University of California, Los Angeles’ institutional review board (21-001426). This study was registered at ClinicalTrials.gov [NCT05027113].

### Procedures

Participants are being recruited through social media, sending emails to relevant groups, and posting physical flyers in communities with significant POC representation. Considering the current COVID-19 pandemic, data are being collected using an online procedure (ie, Qualtrics) at baseline (ie, randomization or week 0), midtreatment (ie, 2 weeks after randomization), and posttreatment (ie, 4 weeks after randomization) via online questionnaires. These assessments were piloted among POC to improve survey clarity and minimize participant fatigue before starting recruitment. These remote assessment strategies have shown to be effective in app-based intervention research with low-income POC [53].

Participants in both conditions will receive a free subscription to the mindfulness meditation app intervention as an incentive to participate. Additionally, participants will be compensated with US $10, $15, and $25 for completing baseline, midtreatment, and posttreatment questionnaires, respectively. There is evidence that monetary compensation significantly reduces attrition in app-based mindfulness meditation studies [49]. Figure 1 shows the study design flow.

**Figure 1 figure1:**
[figure not shown]
Study flow diagram.

### Mindfulness Meditation Intervention

This study will use the Ten Percent Happier app, a consumer-based mindfulness meditation app that offers a wide range of meditation practices developed and guided by renowned experts in the field. Among the many mindfulness apps available in the market, we chose this app because it has been shown to be an effective intervention to increase mindfulness and decrease anxiety and depressive symptoms in previous studies [60-62]. It is important to note that samples in these studies were almost exclusively non-Latinx White.

The intervention will consist of using the Ten Percent Happier app to complete at least 1 meditation daily—with the possibility of exceeding this goal by choosing additional meditations—for 4 weeks. More specifically, participants will be asked to complete The Basics and The Basics II courses to familiarize themselves with the principles of mindfulness meditation. Each audiorecorded session begins with a short video providing psychoeducation around mindfulness meditation and teaching specific techniques (eg, using the breath as an anchor, redirecting attention, noting thoughts and emotions). These 2 introductory courses comprise 15 sessions, in which the meditation length gradually increases from 5 to 17 minutes. For the last 2 weeks of the program, participants will be invited to complete the Essential Advice course, which dispels common myths around mindfulness meditation (eg, “meditators empty their minds,” “successful meditations are those without distractions”) and teaches participants how to deal with common obstacles in their practice (eg, difficult emotions, strong physical sensations). This additional course comprises 14 sessions ranging in length from 15 to 18 minutes. For any additional practice, participants will be able to select any meditation from the Ten Percent Happier library based on their preferences. This highly structured 4-week introductory course may be more likely to provide the foundation necessary for participants to benefit from mindfulness meditation compared with less structured programs often seen in app-based mindfulness meditation research [46]. Moreover, short-term app-based mindfulness meditation interventions (ie, 4 weeks or less) lead to lower attrition rates compared with longer programs [49].

Given the evidence of low treatment adherence in self-directed app-based mindfulness meditation [49-51], we will use a combination of app and text messaging reminders. The Ten Percent Happier app allows users to set a daily notification that can be personalized. Similarly, users will receive daily text messages reminding them to complete their daily meditation. Similar procedures have been hypothesized to foster a therapeutic relationship that keeps the user engaged and promotes a sense of accountability [50,52]. Text messaging reminders have proven effective in increasing treatment adherence among POC community samples [54-56,63], including those in app-based mindfulness meditation studies [49].

### Measures

#### Screening

##### Race-Related Stress

The 22-item IRRS-B [4] measures multiple sources of race-related stress, including individual, institutional, and cultural sources. Participants rate items on a scale ranging from 0 (this never happened to me) to 4 (this event happened and I was extremely upset), with higher scores indicating more race-related stress. Items include “You notice when POC are killed by the police, the media informs the public of the victims’ criminal record or negative information in their background, suggesting they got what they deserve,” “You have been subject to racist jokes by non-POC people in positions of authority and did not protest for fear they might have held it against you,” and “You were refused an apartment or other housing; you suspect it was because you are a POC.” The IRRS-B was developed with a POC sample (ie, Black individuals), showing adequate reliability (α=.78) for both cultural and individual subscales and acceptable reliability (α=.69) for the institutional subscale. The wording of the IRRS-B will be slightly adapted to capture the experience of multiple POC groups rather than only Black individuals. For study inclusion, participants need to obtain a score of 55 (range 0-88), which represents elevated race-related stress.

##### Perceived Discrimination

The 8-item MDM [59] measures perceived discrimination across different racial, ethnic, and cultural groups. Participants rate items on a scale ranging from 1 (never) to 4 (often), with higher scores indicating more levels of perceived discrimination. Items include “How often have you been treated with less respect than other people?” “How often have people acted as if they think you are not smart?” and “How often have you been threatened or harassed?” The MDM was developed using a sample representative of the US population (approximately 40% POC) and has shown good internal consistency (α=.81-.88) in a previous study [59]. For study inclusion, participants need to obtain a score of 12, which represents the 75th percentile of the population distribution.

#### Primary Outcomes

##### Stress

The 10-item Perceived Stress Scale (PSS) [64] is the most widely used measure of perceived stress. Participants rate items on a scale ranging from 0 (never) to 4 (very often), with higher scores indicating more stress. The measure includes items such as “How often have you felt that you were unable to control the important things in your life?” “How often have you felt confident about your ability to handle your personal problems?” and “How often have you been able to control irritations in your life?” The PSS has shown good reliability (α=.84-.86) and validity [64], and it is commonly used in mindfulness meditation research [22]. The PSS will be administered at baseline, midtreatment, and posttreatment.

##### Anxiety

The General Anxiety Disorder (GAD-7) scale [65] is one of the most widely used measures of anxiety symptoms. Participants rate items on a scale ranging from 0 (not at all) to 3 (nearly every day), with higher scores indicating more severe anxiety symptoms. The scale includes items such as “Feeling nervous, anxious or on edge,” “Not being able to stop or control worrying,” and “Feeling afraid as if something awful might happen.” The GAD-7 has shown good internal consistency (α=.89-.90) and validity in POC samples [66]. The GAD-7 will be administered at baseline, midtreatment, and posttreatment.

##### Depression

The 8-item Patient Health Questionnaire (PHQ-8) [67] is one of the most widely used measures of depressive symptoms. Participants rate items on a scale ranging from 0 (not at all) to 3 (nearly every day), with higher scores indicating more severe depressive symptoms. This measure includes items such as “Little interest or pleasure in doing things,” “Feeling down, depressed, or hopeless,” and “Feeling bad about yourself or that you are a failure or have let yourself or your family down.” Although the PHQ-8 omits an item assessing suicidal ideation and self-harm, meta-analytic work shows this version is practically equivalent to the original PHQ-9 measure [68]. The PHQ-8 has good reliability (α=.86-.89) and has shown validity across different racial and ethnic groups [69]. The PHQ-8 will be administered at baseline, midtreatment, and posttreatment.

#### Secondary Outcomes

##### Mindfulness

The 15-item Mindful Attention Awareness Scale (MAAS) [70] measures mindfulness. Participants rate items using a scale ranging from 1 (almost always) to 6 (almost never), with higher scores indicating more mindfulness. Items include “I find it difficult to stay focused on what’s happening in the present,” “I tend not to notice feelings of physical tension or discomfort until they really grab my attention,” and “I could be experiencing some emotion and not be conscious of it until sometime later.” The MAAS is one of the most used measures of mindfulness [71], showing good internal consistency (α=.80-.87) during its development [70]. The MAAS will be administered at baseline, midtreatment, and posttreatment.

##### Self-compassion

The 12-item Self-Compassion Scale–Short Form (SCS-SF) [19] measures self-compassion. Participants rate items using a scale ranging from 1 (almost never) to 5 (almost always), with higher scores indicating more self-compassion. Items in this measure include “I try to be understanding and patient toward those aspects of my personality I don’t like,” “I try to see my failings as part of the human condition,” and “When I’m going through a very hard time, I give myself the caring and tenderness I need.” In the development study of the SCS-SF, this scale showed good internal consistency (α=.86) and validity in a sample with significant POC representation [19]. The SCS-SF will be administered at baseline, midtreatment, and posttreatment.

##### Experiential Avoidance

The 15-item Brief Experiential Avoidance Questionnaire [25] measures experiential avoidance. Participants rate their responses on a scale ranging from 1 (strongly disagree) to 6 (strongly agree), with higher scores indicating more experiential avoidance. Items include “I’m quick to leave any situation that makes me feel uneasy,” “I would give up a lot not to feel bad,” and “I work hard to keep out upsetting feelings.” The BAEQ has shown good internal consistency (α=.80-.86) and construct validity [25]. The BAEQ will be administered at baseline, midtreatment, and posttreatment.

##### Rumination

The 5-item brooding subscale of the short version of the Ruminative Response Scale (RRS-SF) [27] measures rumination. Participants rate their responses on a scale ranging from 1 (almost never) to 4 (almost always), with higher scores indicating more rumination. Items include “Why can’t I handle things better?” “Why do I have problems other people don’t have?” and “What am I doing to deserve this?” The RRS-SF brooding subscale has shown adequate internal consistency (α=.79) and validity in studies with POC samples that experience discrimination [72]. This subscale will be administered at baseline, midtreatment, and posttreatment.

##### Emotion Suppression

The 4-item expressive suppression subscale of the Emotion Regulation Questionnaire (ERQ) [28] measures emotion suppression. Participants rate their responses on a scale ranging from 1 (strongly disagree) to 7 (strongly agree), with higher scores indicating more emotion suppression. Items include “I keep my emotions to myself,” “When I am feeling positive emotions, I am careful not to express them,” and “I control my emotions by not expressing them.” The expressive suppression subscale of the ERQ has shown adequate reliability (α=.68-.76) and validity in samples with significant POC representation [28]. Furthermore, this subscale has been used in mindfulness research with POC [29]. The ERQ will be administered at baseline, midtreatment, and posttreatment.

#### Descriptive Outcomes

##### Acceptability and Appropriateness of the Intervention

The Attitudes Toward Psychological Online Interventions (APOI) [73] is a 16-item measure of experiences with digital interventions with 4 subscales (ie, skepticism and perception of risks, confidence in effectiveness, technologization threat, anonymity benefits). Participants rate items on a scale ranging from 1 (totally agree) to 5 (totally disagree), with higher scores indicating more perceived acceptability and appropriateness. The skepticism and perception of risks subscale includes items such as “By using the app, I do not expect long-term effectiveness” and “It is difficult to implement the suggestions of the app effectively in everyday life.” The confidence in effectiveness subscales contains items such as “I have the feeling that the app can help me” and “I believe that the concept of app interventions makes sense.” The technologization threat subscale includes items such as “I am more likely to stay motivated with a therapist rather than when using an app” and “I learn skills to better manage my everyday life from a therapist rather than from an app.” The anonymity benefits subscale has items such as “An app is more confidential and discreet than visiting a therapist” and “I would be more likely to tell my friends than I use an app than that I visit a therapist.” The APOI has shown good reliability (α=.83) and validity in a previous study [74]. The wording of the APOI will be slightly modified to refer to app-based interventions rather than online interventions. The APOI will be administered to participants in the intervention group at baseline, midtreatment, and posttreatment.

##### Treatment Satisfaction

The 7-item satisfaction with therapy subscale of the Satisfaction with Therapy and Therapist Scale–Revised [75] assesses treatment satisfaction with the app program. Participants rate items on a scale ranging from 1 (strongly disagree) to 5 (strongly agree), with higher scores showing more treatment satisfaction. Examples of items include “I am satisfied with the quality of the therapy I received,” “My needs were met by the program,” and “I would recommend this program to a friend.” The satisfaction with therapy subscale has shown excellent reliability (α=.92) and validity in a digital intervention study with a racially and ethnically diverse sample [76]. The wording of the satisfaction with therapy subscale will be adapted to suit the app-based format of the intervention better. The satisfaction with therapy subscale will be administered to participants in the intervention group at baseline, midtreatment, and posttreatment.

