Those individuals who meet eligibility criteria will be contacted by a research team member to obtain verbal consent and randomize them to either the intervention group (n=40) or a wait-list control group (n=40) using block randomization. During this onboarding procedure, participants in the intervention group will be assisted in installing the mindfulness meditation app, setting app notifications, understanding daily text messaging reminders, and getting familiar with the intervention content. Similar onboarding procedures have been shown to improve treatment adherence in app-based mindfulness meditation studies [49,51]. Participants in the control condition will be reminded of the scheduled assessments and when they will receive access to the mindfulness meditation app (ie, 4 weeks after randomization). Individuals who endorse self-harm or suicidal ideation during the onboarding procedure or in their replies to the text messages will be further assessed and referred to crisis support services.

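### Two baseline scales go only to the intervention arm, so part of baseline follows allocation, and nothing written secures that the self-reported outcomes come before it

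*Protocol article*

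**What the plan says.** All places are in the protocol article.

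- **Treatment Satisfaction:** "The satisfaction with therapy subscale will be administered to participants in the intervention group at baseline, midtreatment, and posttreatment". One of the example items is "I am satisfied with the quality of the therapy I received".
- **Acceptability and Appropriateness of the Intervention:** "The APOI will be administered to participants in the intervention group at baseline, midtreatment, and posttreatment".
- **Procedures:** the assessments are dated "baseline (ie, randomization or week 0), midtreatment (ie, 2 weeks after randomization), and posttreatment (ie, 4 weeks after randomization").
- **Participants:** eligible people are "contacted by a research team member to obtain verbal consent and randomize them to either the intervention group (n=40) or a wait-list control group". In the same onboarding step, "participants in the intervention group will be assisted in installing the mindfulness meditation app", and controls are told when their access will begin.
- **Treatment Adherence:** the app-use indicators are collected at midtreatment and posttreatment only.
- **Results:** baseline is one level of the time factor, and the main interest is the group-by-time interaction. Acceptability, satisfaction and adherence are summarized descriptively.

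**The concern.** There are two linked problems.

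The first needs no inference. A satisfaction scale about treatment received is scheduled at a time when no treatment has been received. Adapting the wording to an app format does not give the participant anything to rate.

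The second concerns the order of steps. A questionnaire set that differs by arm at baseline shows that at least some baseline forms are issued after allocation. The account of the onboarding contact leaves no visible place for the outcome questionnaires before the arm is disclosed. All three primary outcomes are self-reported, and the comparison is an open one between an app now and a wait. Someone who has just learned which of these applies may answer the PSS, GAD-7 or PHQ-8 differently. The effect is read as differential change from baseline, so a shift confined to that first measurement would enter the estimate. The random intercepts named in Results would not remove it.

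**Working it through.** **Order of steps.** The article gives no figure that tests this point, so the sections have to be read together.

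1. Before onboarding there is an online screening questionnaire (Participants). The only instruments listed under Screening are the IRRS-B and the MDM. No outcome measure is placed there.
2. Consent is first obtained at the contact with the research team member. Randomization follows in the same sentence.
3. That same contact discloses the arm: one group installs the app, and the other is reminded when it will get access.
4. Procedures equates baseline with randomization or week 0. This fixes a time point. It does not say whether the questionnaire comes before or after the draw.
5. The APOI and the satisfaction subscale go to the intervention group only, at baseline. Those two forms must come after the draw.

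Steps 1 to 4 name no point between consent and disclosure at which the outcome questionnaires are completed. Step 5 shows that part of the battery is completed later. Post-disclosure completion of the outcomes is therefore a fair reading, but not a stated fact.

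**How a shift would act.** Let the reaction to allocation move one arm's mean by *b* SD at baseline, with a fraction *p* of it still present at posttreatment. The difference in change is then biased by *pb* − *b* = −(1 − *p*)*b*. If the reaction has gone by follow-up (*p* = 0), the bias has the full size *b*. If it persists unchanged (*p* = 1), it cancels.

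**Illustration of size for *p* = 0.** Inputs:

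- Correlation among repeated measures 0.60 (Participants).
- 40 per arm (Participants). As a second case, 30 per arm, because 80 × (1 − 0.24) = 60.8 remain after the planned 24% attrition.
- Two-sided 5% test, normal approximation (assumed).
- *b* from 0.05 to 0.3 SD (assumed; the article gives no value).

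Standard error of the difference in change, in SD units: √(2(1 − 0.60)) × √(2/n).

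- n = 40: 0.894 × 0.224 = 0.200
- n = 30: 0.894 × 0.258 = 0.231

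Type I error = 1 − Φ(1.96 − *b*/SE) + Φ(−1.96 − *b*/SE). For *b* = 0.1 and n = 40, *b*/SE = 0.5, so the error is 1 − Φ(1.46) + Φ(−2.46) = 0.079.

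| Assumed shift *b* (SD) | 40 per arm | 30 per arm |
|---|---|---|
| 0 | 5.0% | 5.0% |
| 0.05 | 5.7% | 5.5% |
| 0.1 | 7.9% | 7.2% |
| 0.2 | 17.0% | 13.9% |
| 0.3 | 32.3% | 25.5% |

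These figures are for the single baseline-to-posttreatment contrast, not for the full three-occasion interaction test.

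**The case against.** The strongest reply is that the article never says the outcome baselines follow allocation. Baseline is given as a time point, the flow diagram is not available here, and a condensed article may leave the sequence of forms to the full protocol. The intervention-only scales date only themselves: the PSS, GAD-7, PHQ-8 and mediators could be completed first, with a short extra module after onboarding. The satisfaction schedule may even be a drafting slip, since the same three-occasion ending closes most of the measure descriptions. This stands in part. It rules out calling contamination established. It does not remove the error in the satisfaction schedule, and it does not show that the outcomes come first.

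A reader might infer more than the article supports:

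- **That the change scores are in fact contaminated.** Neither the order nor any shift is documented.
- **That the bias is 50% to 100% of the planned effect.** This divides an assumed 0.1 to 0.2 SD by the stated d = 0.2. The numerator has no source in the article.
- **That the bias favours the app.** The direction is unknown. Relief in the app arm would lower its baseline and work against the intervention.
- **That baseline adjustment is invalidated.** Results names demographic covariates only.
- **That people who skip a late baseline leave the intention-to-treat set.** Results includes everyone allocated, and a multilevel model can use their later observations.
- **That baseline satisfaction would be carried forward as a dropout's final score.** Carrying forward is described for the intention-to-treat group comparisons. Satisfaction is measured in one arm and only described.

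**Conclusion.** The point holds in two parts. The first is certain: the baseline satisfaction assessment is wrongly scheduled. Its reach is small, because the scale is descriptive and does not enter the efficacy models. The second is conditional: Participants, Procedures and the two arm-specific schedules, taken together, leave the self-reported baselines open to completion after disclosure. They must be reconciled. If that is the order in practice, a non-persisting reaction to allocation biases the group-by-time contrast by an unknown amount in an unknown direction. The 8% to 17% type I error with 40 per arm rests on an assumed 0.1 to 0.2 SD shift that is gone by posttreatment, the article's correlation of 0.60, and a normal approximation. It shows how sensitive the contrast is and does not estimate a bias in this trial. The change is worth making because it costs little and a compromised baseline cannot be collected again.

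**What to change.** 1. State, and apply to all remaining participants, that every baseline outcome and mediator questionnaire is submitted after consent and before allocation is drawn and disclosed.
2. Remove the satisfaction subscale from baseline and keep it at midtreatment and posttreatment, as is already done for adherence.
3. Either give the APOI to everyone before allocation or start it at midtreatment in the intervention arm.
4. For people already enrolled, compare survey time stamps with the time of disclosure and report by arm how many baselines came afterwards. Keep all randomized participants in the main analysis. Leaving out late baselines selects on something that happened after randomization, so it can only be a sensitivity analysis.

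The cost is reordering the online forms, one changed step in the onboarding contact and a minor amendment. Recruitment began in October 2021, so the reordering helps only those not yet randomized.
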